**Fig. 1 Fig1:**
[figure not shown]
Work flow of the study and and the cluster-randomised stepped-wedge design. The Stepped-Wedge design means that at the start all 8 MPHC will deliver the control pathway for the first 2 months as represented with the table in green and blue below. Then, every 2 months 2 new MPHC will switch to the interventionnal pathway. Finally, for the last 2 months, all MPHCs will deliver the interventionnal pathway

### Interventions and comparisons, Fig. 1 and Table 1

**Table 1. Tab1:**
[figure not shown]
*Summary of outcomes and data collection. In blue visits that concerne all groups, in green visits that are only for the intervention group*

^1^ Echelle de Motivation envers l'Activité Physique en contexte de Santé (EMAPS), scale measuring basic psychological needs, scale measuring perceived competence to engage in a personalized physical activity program, scale measuring perceived vitality and energy level, and the self-esteem scale

In Stage 1, all participants are informed about benefits of PA and risks of SED [21] through video capsules made available to all included patients throughout the study. The videos cover definitions of PiA and SED, the short-, medium-, and long-term health impacts of regular PA, the health impact of SED and how to move more and move for longer. A hotline will address any patient inquiries.

The objectives of Stage 2, reserved for the intervention group, are to assess the functional abilities of patients to personalize the support provided. This involves a 2-hour individual appointment with a trained PT from the MPHC and the patient. The Stage 2 appointment includes a 30-minute physiotherapy functional assessment (details of the assessment provided in supplementary material-B) and a 90-minute serious game co-constructing actions through 4 phases of gameplay (details of the game provided in supplementary material). The first phase of the game, the diagnostic phase, focuses on a motivational diagnosis of behaviour change regarding PA and SED and lasts 30 min. Then, the projection phase involves sensitization to action planning and anticipation of obstacles and lasts 30 min. Finally, the commitment phase focuses on the implementation and planning of challenges related to PA and SED for the remaining 15 min.

Stage 3 consists of two follow-up sessions at M2 and M4. The aim of these two 30-minute teleconsultation sessions are to highlight the patient’s successes and failures over the past period and work on the causal attribution (internal/external - modifiable/non-modifiable - controllable/uncontrollable) of successes and failures with the patient. The objectives defined in stage 2 are adapted if necessary and discussed. The PT providing Stage 2 will be the same to provide the M2 and M4 teleconsultation follow-ups for this patient (Stage 3).

#### Statistical analysis

A stepped-wedge design (Fig. 1) with 5 time periods and 4 steps, involving 8 centres transitioning from the control period to the experimental period (2 centres per step), with an average of 20 patients per centre (approximately 4 patients per centre per time period), results in a total sample size of 160 patients.

This design provides 82% power to detect a significant difference between the groups at the first level of the hierarchy (PASS v22, NCSS, LLC, Kaysville, Utah, USA). This calculation is based on the method described by Hemming et al. [22], which uses a linear mixed-effects model with time as a fixed factor at T levels and inter-cluster variation modelled as a random effect. The test statistic employed is a two-sided z-test. Our assumptions leading to this conclusion are that the intervention increases the proportion of patients changing their physical activity profile, corresponding to the first level of the hierarchy, by 20% (in absolute value), assuming that 10% of patients in the control period will experience an improvement. The intraclass correlation coefficient (ICC) is 0.01, and the significance level of the test is 0.05.

For each of the two groups, qualitative variables will be described by their count and percentage, while quantitative variables will be characterized by their mean and standard deviation, or median and interquartile range if they do not follow a normal distribution. The normality of quantitative variables will be assessed by graphical inspection and the Shapiro-Wilk test. The primary analysis does not plan to impute missing data. However, we propose the following strategy currently recommended [23] to minimize the impact of missing data as much as possible: reduce attrition to a minimum by limiting constraints (number of site visits, etc.), continue patient follow-up and outcome collection even in cases of protocol deviations, and consider sensitivity analyses on the per-protocol population, as well as on the ITT population after replacing missing data by multiple imputation methods, provided the assumption of missing at random (MAR) is credible.

A detailed statistical analysis plan will be drafted before the database lock. It will take into account any protocol amendments or unexpected events that occurred during the study and impacted the analyses presented above. The planned analyses may be supplemented in alignment with the study objectives.

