**Methods:**

We designed a prospective, multicentre, cluster-randomised, controlled, step-wedge study. Adult patients without chronic illnesses will be recruited in 8 multi-professional health centres. They will receive educational content on PiA/SED. During the intervention periods, patients will see a physiotherapist for a functional assessment, and an intervention aimed at improving PiA/SED using a serious game. Two follow-up appointments at months 2 and 4 (M2-4) are planned to maintain patient motivation. At M6, a 7-day actimetry will be performed, and at M6-12, questionnaires and semi-structured interviews will close the study. Two primary endpoints will be analysed using a pre-specified hierarchical sequential analysis: the proportion of patients changing PiA/SED at M6. Secondary objectives include: 1-describing changes in PiA/SED at M6 and M12, 2-exploring the link between patient characteristics and changes in PiA/SED, 3-describing participants’ quality of motivation, satisfaction of basic psychological needs, feelings of self-efficacy, perceived levels of vitality and energy, and self-esteem, 4-describing the strategies, barriers and facilitators of behavioural changes, 5-studying the correlation between questionnaires measuring physical activity and actimetry, 6-identifying the perceived barriers and facilitators to implement this care pathway. Assuming that 10% of patients in the control period will improve their PA and that the intervention will increase it by 20%, 160 patients provides 82% power to observe a significant difference.

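### The 82% power does not follow from the plan's own 10% and 30% rates: under the stated model, 160 patients give about 61% (58–63%)

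*Protocol article*

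**What the plan says.** The Statistical analysis section of the protocol article sets out the layout: "A stepped-wedge design (Fig. 1) with 5 time periods and 4 steps, involving 8 centres transitioning from the control period to the experimental period", two centres per step, "with an average of 20 patients per centre (approximately 4 patients per centre per time period"), which "results in a total sample size of 160 patients". The legend of Fig. 1 fixes the rollout: all centres begin under control, "Then, every 2 months 2 new MPHC will switch to the interventionnal pathway", and all are under intervention in the last two months.

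The effect assumption is a rise "by 20% (in absolute value"), "assuming that 10% of patients in the control period will experience an improvement", that is, 10% against 30%. The ICC is 0.01 and the significance level 0.05. The named method is a linear mixed model with time as a categorical fixed effect, a random effect for cluster, and a two-sided z-test.

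The conclusion is "This design provides 82% power to detect a significant difference between the groups at the first level of the hierarchy". The Methods paragraph of the Abstract repeats it: "160 patients provides 82% power to observe a significant difference". Neither place says which outcome variance was used.

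**The concern.** For a yes/no outcome the variance is set by the proportion. The plan assumes two proportions, so it implies two variances: 0.09 under control and 0.21 under intervention. A power figure that uses only the smaller one treats intervention patients as if 10% of them improved, which contradicts the effect being powered for.

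Power for the first endpoint matters twice. It is the chance of detecting the planned effect on physical activity. Under the fixed testing order in the section on the primary aim and outcomes, it also controls access to the second endpoint: if the physical activity test fails, there is no formal test of sedentary behaviour.

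**Working it through.** **Inputs, all from the Statistical analysis section and the Fig. 1 legend.** I = 8 centres, T = 5 periods, m = 4 patients per centre-period (8 × 5 × 4 = 160), two centres switching at each of four steps, difference 0.20, ICC 0.01, two-sided 0.05 (z = 1.96).

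**Layout constants.** The centres spend 4, 4, 3, 3, 2, 2, 1 and 1 periods under intervention.
- U, the number of intervention centre-periods: 20 of 40.
- W, the sum over periods of the squared number of centres under intervention: 0 + 4 + 16 + 36 + 64 = 120.
- V, the sum over centres of the squared number of intervention periods: 2 × (16 + 9 + 4 + 1) = 60.

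**Formula** (closed-form variance of the treatment effect for the model described). With total individual variance v, let s² = (1 − 0.01)·v/4 and t² = 0.01·v. Then

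Var = I·s²·(s² + T·t²) / [(I·U − W)·s² + (U² + I·T·U − T·W − I·V)·t²]

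The bracketed coefficients are 8 × 20 − 120 = 40 and 400 + 800 − 600 − 480 = 120. Power = Φ(0.20/√Var − 1.96).

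**Reproducing the plan's figure, v = 0.10 × 0.90 = 0.09 for everyone.** s² = 0.022275 and t² = 0.0009. The numerator is 8 × 0.022275 × 0.026775 = 0.004771 and the denominator 40 × 0.022275 + 120 × 0.0009 = 0.999. Var = 0.004776, SE = 0.0691, 0.20/SE = 2.894, power = Φ(0.934) = 82.5%. If 0.09 is taken as the residual rather than the total variance, power is 82.1%. Either way this is the printed 82%.

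**Using both assumed rates.** The intervention variance is 0.30 × 0.70 = 0.21, and it applies to 20 of the 40 centre-periods.

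| Treatment of the variance | SE | Power |
|---|---|---|
| Mean of 0.09 and 0.21 (0.15) | 0.0892 | 61.1% |
| Pooled proportion 20% (0.16) | 0.0921 | 58.3% |
| Separate variance per condition, generalised least squares (t² from 0.0021 to 0.0009) | 0.089–0.087 | 61.2–63.2% |

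For the first row: s² = 0.037125, t² = 0.0015, Var = 0.013254/1.665 = 0.00796, 0.20/SE = 2.242, power = Φ(0.282) = 61.1%.

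The SE is therefore 0.087–0.092, about 26–33% larger than 0.069.

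**Simulation.** 20,000 simulated trials with binary outcomes at these rates, analysed by generalised least squares at the planned ICC and a z-test, rejected in 61.6% of runs (5.7% under no effect).

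**Could another input explain 82%?** With variance 0.15 and one input changed at a time: ICC of 0 gives 63.7%; a one-sided test 72.5%; 5 patients per centre-period 70.1%; no period effects 89.7%. None gives 82%.

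**Difference detectable with 80% power at 160 patients.** With mean variance, 10% against 36% gives 80.5%. With pooled variance, 36% gives 76.5%, 37% gives 78.9% and 38% gives 81.2%. The answer is 26 to 28 points, depending on the convention.

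**The case against.** The article names its software, method, model and test, but not the variance entered, and the cited method paper is not available here. A linear mixed model for a binary outcome uses one residual variance in its usual closed form, so choosing a single value is partly a convention of the stated method. A reader might go further and conclude that the sponsor demonstrably entered the control variance, or that 82% can arise in no other way. The documents support neither. The use of 0.09 is inferred from the numerical match. A parallel cluster calculation (80 per arm, design effect 1 + 19 × 0.01 = 1.19) comes close at 83.4%, although it is not the method described, because it ignores the stepped rollout and the period effects.

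What stands is that the cause is unproven. What does not stand is the 82%. A single variance is acceptable if it represents both conditions, and then it is 0.15 or 0.16. The averaged, pooled and condition-specific calculations and the simulation all fall between 58% and 63%.

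Two further inferences should also be resisted. Nothing in the article says how a non-significant result would be interpreted, so a claim that it would be misread is speculation. Nor does the correction itself oblige the sponsor to enlarge the trial; it corrects a stated number.

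**Conclusion.** The point holds: the stated power is about 20 percentage points too high for the stated inputs. With 10% against 30% it is about 61% (58–63% by variance convention), and the chance of missing the assumed effect is about 39% (37–42%), not 18%. Failure on physical activity would also close the formal test on sedentary behaviour.

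The result rests only on the printed design, rates, ICC, test and model, and on the binomial variances that those rates imply. It takes all 160 patients as analysed. It does not depend on knowing which variance was entered in the software.

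**What to change.** Re-run the calculation with the binomial variance of each condition (0.10 × 0.90 and 0.30 × 0.70) and state the variance convention. Replace 82% in the Abstract and in the Statistical analysis section by about 61% (58–63%). Add the difference detectable with 80% power at 160 patients: about 26 to 28 points, that is, 10% against 36–38%.

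The cost is wording, and a stated power that is less favourable. No added patients are required. If the sponsor finds 61% too low and wants at least 80% for the original 20-point effect, the same formula gives about 7 patients per centre-period, 8 × 5 × 7 = 280 in total (82.8% with variance 0.15, 80.3% with 0.16). That would be a separate design decision.

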## Discussion

Healthcare professionals in primary ambulatory care, including GPs and PTs, are already involved in tertiary prevention and can also contribute to primary and secondary prevention, particularly in the domain of PA^9^. With their expertise in assessment, support, and goal customization, they can increase opportunities for prevention before patients develop long-term conditions.

The preventive dimension of the study, the personalized and participatory nature of the intervention, and the prediction of success/failure through data analysis allow to fulfil the requirements of 4P medicine—preventive, personalized, predictive, and participatory—in primary ambulatory care.

This project is original, innovative, and promising due to its pragmatism and anticipated feasibility in primary ambulatory care, the involvement of healthcare providers in primary-secondary prevention, the multi-professional collaboration involving screening/motivation by the GP and intervention by the PT, an intervention based on current theoretical behaviour change models and a pathway combining face-to-face and online support allowing personalisation of the intervention by a trained PT. Additionally, the use of a stepped-wedge design allows to harmonise the competence of all professionals in motivational support for PA and provide information about the risks associated with PiA/SED. This has two main benefits. First, it allows for a strict control of the effect of the personalised intervention given all participants will have access to information about the benefits of PA and risks of PiA/SED. Second, at the end of the trial, all investigators will have benefited from specialised training in primary prevention of SED/PiA. This would not have been the case in a parallel cluster randomised trial.

Patients will truly be active participants in their behaviour change as the intervention aims to meet the three fundamental psychological needs: need for autonomy: the patient sets their own challenges and activities; need for social relatedness: support from trained and supportive professionals; and need for competence: adapting challenges to the patient’s skills and defining intermediate challenges will help maintain the patient in a context of success.

## Data Availability

No datasets were generated or analysed at this stage.
